#### Sleep quality

As a validated child-report measure of sleep quality is not available, a single item on sleep quality was adapted for children from the Pittsburgh Sleep Quality Index (PSQI) specifically for this study. The wording of the adaptation was developed by consensus across three psychologists who specialise in sleep and tested in children aged 10 to 12 years old (N = 5). The question asks children to: ‘Rate how well you have been sleeping over the last month’, with responses ranging from ‘Very well’ (0) to ‘Not at all well’ (3).

### Measures of mechanisms

All potential mechanisms will be measured at all four assessments (baseline, primary, secondary, and tertiary endpoints) and explored as mediators of change.

#### Dysfunctional beliefs about sleep

To determine the effect of the intervention on dysfunctional beliefs about sleep and explore its role as a potential mediator, The Dysfunctional Beliefs and Attitudes about Sleep for Children (DBAS-C10) questionnaire [42] will be used. It contains 10-child-reported items measuring dysfunctional beliefs about sleep. Items are rated on a Likert scale from (1) Strongly Disagree to (5) Strongly agree [42]. The DBAS-C10 has been adapted for use with children and has demonstrated validity and reliability [43].

#### Pre-sleep arousal, and pre-sleep cognitions

The Sleep Anticipatory Anxiety Scale – Adolescent Version (SAAQ) [44] is a child-reported measure of anxiety levels before going to bed or during the pre-sleep period. The SAAQ assesses the intensity of anxiety symptoms related to sleep, including worry, restlessness, and anticipatory thoughts via three subscales: Somatic, Sleep-related Cognitions and Rehearsal/Planning. Each item is scored on a 4-point Likert scale ranging from Strongly Disagree (1) to Strongly Agree (4). The scale measures the degree of anxiety individuals may experience in relation to sleep and is widely used in youth samples with demonstrated validity and reliability [45].

#### Repetitive negative thinking

The Persistent and Intrusive Negative Thoughts Scale (PINTS) [46] is a 5-item questionnaire that assesses the frequency and intensity of negative thoughts that may contribute to emotional distress in children, adolescents, and adults. The PINTS has demonstrated good internal consistency and reliability in children [47].

### Exploratory outcomes

#### Major depressive disorder

The web-based Kiddie Schedule for Affective Disorders and Schizophrenia (K-SADS-COMP; assessment of mood disorders only) [26] is a commonly used parent-report tool used to assess Diagnostic and Statistical Manual of Mental Disorders-5 (DSM-5) diagnostic criteria [47]. The mood disorder module for childhood psychiatric diagnoses [26] will be used to assess the presence of current at past MDD. While the instrument comprises 22 diagnostic modules, only the assessment of mood disorders will be included in this study taking less than 30 min to complete. It will be administered at baseline and at 9-months post-baseline.

#### Quality of life

The Child Health Utility 9D (CHU-9D) [48] assesses adolescents’ health-related quality of life in nine domains of functioning including worry, sadness, pain, tiredness, annoyance, schoolwork/homework, sleep, daily routine, and ability to join activities. It contains 9-items, with each domain rated on a 5-point scale and higher scores indicating greater severity (e.g., I don’t feel worried today (1) to I feel very worried today (5)). Items are summed to produce a total score ranging from 9 to 45. The scale has good psychometric properties among children (7–17 years) [49] and can estimate quality adjusted life years for use in future cost-effectiveness evaluations of Sleep Ninja. It will be administered at baseline and at 6-weeks post-baseline.

### Other measures

#### Demographic information

At baseline, parents of participants will be asked their child’s date of birth, school grade (Year 4, 5, 6), gender identity (female, male, non-binary, different identity, free response option), whether they identify as Aboriginal or Torres Strait Islander (yes, no, prefer not to say), their Australian state or territory location (NSW, QLD, VIC, TAS, SA, WA, NT, ACT), location description (metropolitan, regional, or rural/remote), and the type of mobile device they use (iOS [e.g., Apple], Android [e.g., Samsung], other). Participants will also be asked how they heard about the study (e.g., social media advertisement, Black Dog Institute website, word of mouth, other) and their motivations for participating (e.g., need for mental health care, desire to contribute to a broader social good, parents/carers encouragement, friend participating, financially motivated, desire to help research, interest in learning about mental health or other).

#### Recent mental health care

At baseline, parents of participants will be asked to report whether their child has ever been diagnosed with insomnia or another mental illness by a health professional (yes – no, I don’t know, I’d rather not say), with an open response option to list the ‘other’ mental illnesses, whether their child has received psychological treatment for insomnia by a mental health professional (yes, no, I’d rather not say) and whether their child has ever taken prescribed or over the counter medication for insomnia (yes, no, I’d rather not say). At the primary, secondary, and tertiary endpoints, parents will be asked the same questions to determine whether throughout the study their child received a diagnosis of insomnia, received psychological treatment from a health professional, started taking medication (prescribed or over-the-counter) for insomnia or felt their child needed mental health support. They will also be asked if their child received a diagnosis of depression or anxiety since the last assessment.

#### Previous use of mobile apps for sleep and expectancies

At baseline, parents will be asked to report whether their child has ever used a mobile app to assist with their sleep (yes, no, I’d rather not say), and how useful they think a mobile app for sleep would be for their child (not at all useful, somewhat useful, neutral, very useful, extremely useful). Parents will also be asked how much they think their child’s sleep or emotional well-being could be improved by using a mental health smartphone app.

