To overcome the lack of accessible CBT-I for older children, our research team has adapted the Sleep Ninja smartphone application [20] for use among children aged 10 to 12 years old. The Black Dog Institute originally developed Sleep Ninja, a free, fully automated CBT-I smartphone application designed in consultation with adolescents and their parents [21], for adolescents aged 12 to 16 years. Sleep Ninja contains six brief lessons or ‘training sessions’ (each up to ten minutes in duration), that deliver core components of CBT-I, including psychoeducation, stimulus control, sleep hygiene, and sleep-focused cognitive therapy. It uses gaming elements to enhance user engagement, which are based on a Ninja analogy with users ‘levelling up’ on completion of a training session until they master sleep skills and become a black belt in sleep.

Previous research shows Sleep Ninja improves insomnia and reduces depression symptoms in adolescents relative to an active control, with superior effects for younger teenagers [17, 22]. Given its gamified features and readability level (i.e., for readers at the Year 5 to 6 level, aged 10 to 12 year old) of the original Sleep Ninja app, and children’s increased capacity to use interactive smartphone applications [23], Sleep Ninja required only minor modifications for adaption for 10 to 12 year olds. The key modifications included involving parents in the intervention by developing a website containing resources for parents, guardians and carers (henceforth referred to as parents) to support their child’s autonomous use of Sleep Ninja, and ensuring the suggested bedtimes were based on age-appropriate sleep duration recommendations [24]. A clinical trial is now needed to determine the effectiveness of Sleep Ninja for improving insomnia symptoms and other mental health symptoms in primary school children aged 10 to 12 years.

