### Participants

Eligible participants are those aged 10 to 12 years old and not yet in secondary school; located in Australia; who own or have access to a smartphone; have access to the Internet, an active email address and mobile phone number; who have age-appropriate English proficiency; and who can obtain their parent’s consent. Eligible participants are also required to be experiencing sleep disturbance, as determined by a total score of ≥ 2 (i.e., indicating 2–3 nights per week) on any of the first 5 items of the Paediatric Insomnia Severity Index (PISI) reported by the parent at screening. Ineligible participants are those who currently meet or have previously met the criteria for a MDD diagnosis as determined by parent report on the mood module of the Kiddie Schedule for Affective Disorders and Schizophrenia (KSADS-COMP) [26] at baseline.

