### Intervention condition

Participants allocated to the intervention condition receive access to the child-adapted version of Sleep Ninja for 6 weeks. Sleep Ninja is an automated smartphone application co-designed with 12- to 16-year-olds and parents to deliver CBT-I. It is free and publicly available in Australia on devices using iOS and Android operating systems. The program includes six sequential modules (referred to as ‘training sessions’), a sleep tracking function, sleep scheduling based on required wake time and age-dependent sleep duration recommendations, personalised wind-down routines and reminders, a series of sleep tips, and general information about sleep. Each training session covers a core CBT-I strategy including: (a) sleep scheduling; (b) stimulus control strategies; (c) sleep hygiene for evenings and daytime; (d) cognitive therapy including how to deal with thoughts that can prevent sleep onset (e.g., repetitive worrying) (e) identification and planning for high-risk situations and diversions from sleep routine; and f) relapse prevention. Sessions are delivered through an automated chat-bot where the Ninja acts as a sleep coach. Sleep Ninja is designed to be used during the day and not at bedtime to prevent device use and blue light interfering with sleep. The child version of Sleep Ninja also includes a website for parents, designed in collaboration with parents. The website contains guidance to assist parents in supporting their child to use Sleep Ninja autonomously and additional resources including information on Sleep Ninja, case examples, frequently asked questions, and contact information for the Child Sleep team at the Black Dog Institute. Parents of participants allocated to receive the intervention will be provided with the URL for the website alongside instructions on how to download Sleep Ninja. Child participants allocated to the intervention condition will be instructed to complete the Sleep Ninja app content by undertaking one ‘training session’ and tracking their sleep for three nights per week (approximately 10 min in duration) for six weeks. One email and one Short Message Service (SMS) reminder will be sent to the parents of participants who fail to download the Sleep Ninja app within 7 days of randomisation. Participants who do not download the app will remain in the trial and be included in the intention-to-treat analyses.

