**ASSESSMENTS**:						
*Primary Outcome*						
**Sleep problems** Paediatric Insomnia Severity Index - Adolescent (PISI-A); Child self-report		X		X	X	X
*Secondary Outcomes*						
**Sleep problems** Paediatric Insomnia Severity Index (PISI); Parent self-report		X		X	X	X
**Depressive symptoms** The Revised Child Anxiety and Depression Scale – 25; Subscale (RCADS-25); Parent self-report		X		X	X	X
The Revised Child Anxiety and Depression Scale – 25; Depression Subscale (RCADS-25); Child self-report		X		X	X	X
**Anxiety Symptoms** The Revised Child Anxiety and Depression Scale − 25; Anxiety Subscale (RCADS-25); Parent self-report		X		X	X	X
The Revised Child Anxiety and Depression Scale – 25; Anxiety Subscale (RCADS-25); Child self-report		X		X	X	X
**Daytime Sleepiness** The Epworth Sleepiness Scale; Child self-report		X		X	X	X
**Sleep Quality** Sleep Quality Question; Child self-report		X		X	X	X
**Dysfunctional beliefs about sleep** The Dysfunctional Beliefs and Attitudes about sleep (DBAS); Child self-report		X		X	X	X
**Pre-sleep hyperarousal and anxiety** The Sleep Anticipatory Anxiety Scale (SAAQ) Adolescent Version; Child self-report		X		X	X	X
**Repetitive Negative Thinking** The Persistent and Intrusive Negative Thoughts Scale (PINTS); Child self-report		X		X	X	X
**Quality of Life** The Child Health Utility 9D (CHU-9D); Child self-report		X		X		
**MDD Diagnosis** Kiddie Schedule for Affective Disorders and Schizophrenia (K-SADS-COMP; assessment of Mood disorders only); Parent self-report		X				X
*Additional study measures*						
**Registration details** Registration Questionnaire; Parent self-report		X				
**Demographics** Demographics Questionnaire; Parent self-report		X				
**Recent mental health care** Mental Health Care Questionnaire; Parent self-report		X		X	X	X
**Previous use of mobile apps for sleep** Mobile app questionnaire; Parent self-report		X				
**Digital program satisfaction** Satisfaction Questionnaire; Child self-report				X		
**Treatment Adherence*** Treatment adherence; Parent self-report				X		
**Withdrawal reasons** Withdrawal question		X	X	X	X	X

*Note.* *Assessed in the intervention group only

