### Recruitment and screening

Trial recruitment will begin in August 2023 and will continue until the required sample size is achieved. This study will utilise an online recruitment strategy targeting parents/guardians of children aged 10 to 12 years as this recruitment method has been established to recruit parents and young people [22]. Study advertisements will be published on the Black Dog Institute’s website and social media channels (Facebook, Instagram, and Twitter) and through Institute communications via established professional newsletters. Paid advertisements will be utilised on social media sites targeting parents (Facebook, Instagram, Twitter, LinkedIn) and Google. The research team will also send two email invitations to adults who have consented to be contacted about research studies conducted at the Institute. Additionally, the research team will contact primary schools via email to share study information with their communities. Contact will also be made by the research team to relevant Australian mental health organisations and services including psychology clinics and parent and youth groups to request distribution of study advertisements through these organisations’ communication channels (e.g., website, newsletters, social media, in-person clinics). Study advertisements will contain a URL directing all interested participants to the study’s webpage where they can review study information, and may choose to commence screening, and provide consent using the provided links. Direct contact between the participant and the study team is not required during recruitment and study enrolment. Parents will complete screening on behalf of the child participant. To ensure participant safety during recruitment and screening, parents of excluded participants will be provided with contact information for Australian mental health and crisis support services and encouraged to seek help if mental health support is required for either themselves or their child. Tips about healthy sleep will also be provided.

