### Limitations

Given Sleep Ninja is publicly available, contamination bias may occur. To minimise the risk of contamination, Sleep Ninja is not named in any of the recruitment or trial information. The use of sleep applications is also being assessed at each assessment to monitor and identify the use of Sleep Ninja by participants in the control condition. Despite these limitations, the results of this trial will offer valuable insights into the potential of a CBT-I smartphone app to address a gap in the current treatment landscape and shed light on the factors that contribute to therapeutic benefits in children aged 10 to 12 years old.

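### Past or current use of Sleep Ninja does not bar entry, and the app-use item as described cannot single it out, so already-exposed children can dilute the comparison

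*Protocol article*

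**What the plan says.** **Eligibility.** The Participants section gives a single ground for ineligibility: "Ineligible participants are those who currently meet or have previously met the criteria for a MDD diagnosis". Neither the inclusion criteria nor this sentence mentions earlier or current use of Sleep Ninja.

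**Availability and recruitment.** The Intervention condition section says of the app: "It is free and publicly available in Australia on devices using iOS and Android operating systems". The Introduction names the developer: "The Black Dog Institute originally developed Sleep Ninja, a free, fully automated CBT-I smartphone application", built for ages 12 to 16. Under Recruitment and screening, "Study advertisements will be published on the Black Dog Institute’s website and social media channels". The same section also lists paid advertising, schools, clinics and other organisations.

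**What is asked about app use.** Under Previous use of mobile apps for sleep and expectancies, parents report at baseline "whether their child has ever used a mobile app to assist with their sleep". The three answers offered are yes, no and a refusal option. In Table 1 the matching row ("Mobile app questionnaire; Parent self-report") is marked at baseline and nowhere else.

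**What the Limitations section adds.** There, the "use of sleep applications is also being assessed at each assessment to monitor and identify the use of Sleep Ninja" by children in the control condition.

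**Allocation and analysis.** Randomisation is automatic and follows directly on the baseline survey (Randomisation). Everyone randomised is analysed by intention to treat (Data collection, management, and statistical methods).

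**The concern.** Exposure before randomisation differs from contamination afterwards, and the protocol deals only with the latter. Concealing the app's name and withholding it from controls until 9 months can stop a control family from finding the app. Neither measure helps if the child already has it.

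Exposure is plausible. Entrants must have disturbed sleep, so their families have had a reason to try a free sleep app. Some will be reached through the developer's own channels. The Introduction says that only minor changes were needed to adapt the app for ages 10 to 12, so earlier use of the public version would be much the same treatment.

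Followed as written, the plan randomises a child who has finished all six sessions, or who uses the app today. In the control arm such a child has already had the experimental treatment; in the intervention arm the child largely repeats it. Either way the difference between arms on the primary outcome would tend to shrink, and the data as described would not show how many such children there were.

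**Working it through.** **1. Can the described data identify a prior Sleep Ninja user?**

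| Place | When | Whom it covers | Names Sleep Ninja? | Keeps a child out? |
|---|---|---|---|---|
| Participants | Screening and baseline | All | No | Only for MDD history |
| Previous use of mobile apps | Baseline | All | No: any sleep app, ever | No |
| Table 1, app questionnaire row | Baseline only | All | Not stated | No |
| Limitations | Each assessment | Control arm, by its stated purpose | Yes, by its stated purpose | No: monitoring |
| Intervention adherence and attrition (in-app data) | During the trial | Described for users of the app under test | Yes | No; no link to pre-trial use described |

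Two results follow. The Limitations section conflicts with Table 1 on timing and with the item's description on content. And no row keeps an exposed child out: the app item is not an eligibility item, so no answer to it stops allocation.

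**2. The plan's own figure.** The point rests on no figure in the plan, but the sample size shows how much room there is for dilution. Inputs (Sample size section): α = 0.05 (sidedness not stated; taken as two-sided), power 0.80, d = 0.41, attrition 40%, total 214.

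- A two-sided comparison of two means at d = 0.41 needs 94 to 95 completers per arm, 188 to 190 in total. Dividing by 0.6 gives 314 to 317, not 214.
- A two-sided t-test at d = 0.50 gives 64 per arm: 128 / 0.6 ≈ 214.
- At d = 0.41, a baseline adjustment with a correlation of about 0.56 would also give 214, but none is stated.

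This mismatch is a separate matter. It is used here only to fix the starting point: 214 × 0.6 ≈ 128 completers, or 64 per arm.

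**3. Dilution.** The documents give no prevalence, so the share f of prior users is an assumption. Further assumptions: f is equal in the two arms, prior users contribute no between-arm difference, and the standard deviation is unchanged. Then

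- diluted effect = 0.41 × (1 − f)
- required sample size rises by 1 / (1 − f)²
- power ≈ Φ(d√(n/2) − 1.96), with n = 64 per arm and no baseline adjustment

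| f (assumed) | Effect | Sample-size factor | Power |
|---|---|---|---|
| 0% | 0.41 | 1.00 | 64% |
| 5% | 0.41 × 0.95 = 0.39 | 1 / 0.9025 = 1.11 | 60% |
| 10% | 0.41 × 0.90 = 0.37 | 1 / 0.81 = 1.23 | 55% |
| 20% | 0.41 × 0.80 = 0.33 | 1 / 0.64 = 1.56 | 46% |

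If the trial was in fact sized on d = 0.50, the same shares take power from 81% to 77%, 72% and 62%.

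**The case against.** **Users cannot be identified at all.** A reader might infer this from the generic baseline item. The document does not support it: the Limitations section states an intention to detect Sleep Ninja use by controls at every assessment, and an article may shorten questionnaire wording. What stands is narrower: the item as described does not deliver what the Limitations section promises, and the schedule contradicts it.

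**A prior user defeats the concealment by recognising the app.** This is also tempting and also unsupported. The Blinding section withholds the name to stop controls from obtaining the app during the trial. Controls are shown flyers, so they have no app to recognise; intervention families are told how to download Sleep Ninja in any case. The real weakness is only that a control child may already have it.

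**The number may be small and the loss overstated.** This is fair. The public version targets ages 12 to 16, and entrants are 10 to 12 and not yet in secondary school. The developer's channels are one recruitment route among several. A prior user may have opened the app once and stopped. The trial version adds a parent website and age-appropriate bedtimes. Entrants must still have disturbed sleep, and the primary contrast is change from baseline, so earlier benefit is already in the baseline score. A zero contribution from prior users is therefore an unfavourable assumption.

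**Enrolling regardless of history is a legitimate choice.** The protocol records past psychological treatment and medication for insomnia without excluding for them. But those are other treatments. Here the exposure is the experimental intervention itself, which the protocol elsewhere takes care to keep from controls.

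**Conclusion.** The point holds as a gap in eligibility together with an inconsistency in how app use is captured. Children who have used, or now use, the tested app can be randomised and stay in the intention-to-treat analysis, and the described item would not separate them from users of other sleep apps.

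The expected consequence is dilution toward no difference. A reader might infer bias between the arms; the design does not support that, because exposure before randomisation is balanced on average by random allocation.

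The size cannot be established from the document. On the unfavourable assumption that prior users contribute no difference, an assumed 5% to 10% share lowers d = 0.41 to between 0.39 and 0.37. That is modest, but the correction costs little and protects the primary contrast.

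**What to change.** 1. In the parent screener, ask which sleep apps the child has used and whether any is used now, as free text or a list of several apps, so that Sleep Ninja is not singled out and its concealment is kept.
2. Add prior or current use of Sleep Ninja to the exclusions in the Participants section.
3. Reconcile Table 1, the description of the app-use item and the Limitations section. If use is to be monitored at each assessment, schedule it there and describe an item that captures Sleep Ninja by name among the apps reported, again with neutral wording.

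The cost is one screener item, one exclusion line and a short repeated item at follow-up. A few families become ineligible.
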